### Statistical Analysis

The statistical analysis plan follows the Consolidated Standards of Reporting Trials (CONSORT) evidence-based reporting guideline to ensure research transparency, specifically to trials of nonpharmacologic treatments (NPTs), as rehabilitation (48). The primary (pain) and secondary (spasticity and rehabilitation parameters) outcome measures, collected at prespecified time point *t*_3_ and *t*_4_ vs. *t*_0_, will be expressed as mean and standard error and assessed for statistically significant differences using independent *t*-test for data normally distributed or Mann–Whitney U test for skewed data. Based on the CONSORT NPT item 12b, the evaluation of the outcome measures over time will be carried out through a linear mixed model. The correlation between pain (VAS measure) and recovery (FMA-UE), assessed at *t*_0_, *t*_1_, *t*_2_, *t*_3_, and *t*_4_, will be performed through the Pearson product-moment correlation coefficient (*r*). In agreement with the CONSORT NPT item 12a, the clustering of data will be performed by blinded care providers of the center. Statistical analysis will be performed using SPSS statistics software (Chicago, IL, USA). Values of *p* < 0.05 will be considered statistically significant.

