### Eligibility Criteria

Consecutive patients, admitted to Sant' Anna Institute with the diagnosis of stroke after hospital discharge will be enrolled, accordingly with the following inclusion criteria:

- First-ever stroke within 24–72 h from diagnosis confirmed through functional MRI scan, regardless of the side, location, and extension of the lesion;-Stroke-related hemiplegic patients of any age at hospital discharge within 48–72 h after stroke with fMRI scan of the area affected;-Severe upper limb impairment, according to the Upper Extremity Subscale of the Fugl–Meyer Motor Assessment [FMA-UE (0-35) (21)];-Absence of hemiplegic upper limb-related baseline pain based on the visual analog scale (VAS), the bedside active examination with a numerical rating and, also, the douleur neuropathique en 4 questions (DN4) for the evaluation of neuropathic prestroke pain.

Exclusion criteria will be:

-Bilateral impairment;-Presence of aphasia;-Presence of cognitive impairment, as assessed using the cognitive assessment scale for patients with stroke (22), to avoid interference of aphasia or hemispatial neglect that may occur with the commonly used Mini-Mental State Examination (23) and Montreal Cognitive Assessment (24);-Stroke diagnosis without the occurrence of hemiparesis of the upper limb;-Previous rehabilitation.

Due to the lack of specific observational tools for poststroke pain in noncommunicative patients, this pilot study will not include patients affected by aphasia and cognitive impairment. The informed consent will be obtained by healthcare operators and patients will be informed about the study and they will be provided with a consent form. No additional consent provisions for biological specimens will be needed since the latter will not be collected.

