### Outcomes

The effect of robot-assisted rehabilitation using ARAMIS on the prevention of the development of poststroke pain is the primary endpoint of the ROBOCOP study. The primary outcome measures consist in the assessment of pain through the VAS, including a bedside active examination and probing of somatosensory functions to test touch, temperature, and pain sensations (26). The development of neuropathic components of poststroke pain will be assessed using the DN4. The secondary endpoints include spasticity, tightly linked to pain and developed by up to 40% of patients with hemiparetic stroke, and clinical motor rehabilitation. Spasticity will be assessed using the Modified Ashworth Scale (MAS) (27) and the Resistance to Passive movement Scale (REPAS), based on the Ashworth scale (28), for major joint movements in upper and lower limbs. Clinical motor rehabilitation will be measured according to the Standardizing Measurement in Arm Rehabilitation Trials [SMART] toolbox of the recommended core set of outcome measures for rehabilitation after stroke (29, 30). The latter includes FMA-UE, the Action Research Arm Test, and the activities of daily living/stroke-specific outcomes of the Barthel Index. The clinical motor rehabilitation will also be characterized through structural and functional MRI scan. In particular, structural MRI is intended to evaluate infarct and injury volume (31) and functional MRI to assess the activation volume in the stroke ipsilateral hemisphere during movement of paretic limb, which is related to the extent of behavioral recovery (32). The connection strength between the ipsilesional primary motor cortex and the contralateral regions will be examined (33).

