### Participant Timeline

Patients will be randomly allocated to the intervention or control group in a 1:1 allocation ratio. The enrollment will last up to the achievement of the sample size. The most important time points for the assessment of pain development are 3 and 6 months poststroke, with the addition of measurement time points in the subacute phase (29, 34). In fact, differences in motor activity of paretic limbs 24–36 h after symptoms onset, and also at 3 and 6 months (35, 36) have been demonstrated. Therefore, the assessment of the primary and secondary outcomes will be conducted at the following time points: baseline measurement at Sant'Anna Institute admission (24–72 h since stroke event) (*t*_0_); 1 month after stroke (*t*_1_), i.e., at half of the rehabilitation period; 2 months after stroke (*t*_2_), i.e., after the completion of neurorehabilitation with ARAMIS in the intervention group and of conventional rehabilitation in the nonintervention group; 3 months (*t*_3_) and 6 months (*t*_4_) after stroke, since the latter are critical for rehabilitation and pain development. Routine clinical and neurophysiological assessments will be performed before and at the end of the treatment. Loss of tolerance to the procedure up to discontinuation will be recorded on a specific form. The schedule of enrollment, interventions, and assessments is reported in Table 1.

**Table 1 T1:** Schedule of enrollment, interventions and assessments according to Standard Protocol Items: Recommendations for Interventional Trials (SPIRIT).

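### Motor (and, less so, spasticity) outcomes at t3 and t4 are compared by an unadjusted two-sample test although each patient's t0 score is collected; the test is valid but gives up precision and leaves chance baseline imbalance in the estimate

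*Protocol article*

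**What the plan says.** The Statistical Analysis section of the Protocol article sets one method for all outcomes. The sentence that does so begins "The primary (pain) and secondary (spasticity and rehabilitation parameters) outcome measures, collected at prespecified time point". It sets the scores at t3 and at t4 against those at t0, and compares the arms by a two-sample t-test when the data look normal and by the Mann–Whitney U test when they are skewed. It names no covariate, and it does not say whether the tested quantity is the follow-up score itself or its change from t0. The next sentence adds that "the evaluation of the outcome measures over time will be carried out through a linear mixed model", without saying how t0 enters that model.

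The secondary measures are MAS and REPAS for spasticity and, for motor recovery, a core set: "The latter includes FMA-UE, the Action Research Arm Test, and the activities of daily living/stroke-specific outcomes of the Barthel Index" (Outcomes). Participant Timeline states that "the assessment of the primary and secondary outcomes will be conducted at the following time points", the first being t0 at admission, 24–72 h after stroke. So each patient's own baseline score will be available.

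Eligibility requires "Severe upper limb impairment, according to the Upper Extremity Subscale of the Fugl–Meyer Motor Assessment", with permitted scores of 0–35. The section on allocation describes minimisation on sex and no other factor.

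**The concern.** A patient's score at t3 or t4 is likely to be related to the score at t0. A comparison that does not model this relation leaves predictable between-patient variation in the error term. It also lets any chance difference between the arms at t0 carry into the estimated effect. Nothing in the allocation scheme balances baseline motor or spasticity score.

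This applies under both readings of the comparison with t0. A raw follow-up score makes no correction for baseline. A change score subtracts baseline with a fixed coefficient of 1, which is too much when the true slope is below 1 and too little when it is above 1.

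At stake is the precision of the declared secondary claims on motor recovery and spasticity. The primary pain outcome is not affected in the same way: pain in the affected limb must be absent at entry, so its baseline has almost no spread to adjust for.

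**Working it through.** **Inputs.** From the documents: 53 per arm before the drop-out allowance, 59 per arm and 118 in total after it (Sample Size); baseline collected at t0 (Participant Timeline); sex as the only balancing factor. Not in the documents and therefore assumed: the baseline-to-follow-up correlation ρ (0.4–0.7) and the ratio of follow-up SD to baseline SD (1, 1.5 and 1.8). A ratio above 1 is plausible for FMA-UE because entry is capped at 35.

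**The plan's own figures.** The plan gives no precision or power figure for the secondary scales, so there is none to reproduce. The 53 per arm was set for the primary outcome and serves here only as the arm size. Its drop-out step checks: 53/0.9 = 58.9, so 59 per arm and 118 in total.

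**Formulas.** With baseline SD s0, follow-up SD s1 and slope β = ρ·s1/s0, the per-patient variances behind the arm difference are:

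- raw follow-up: s1²
- change score: s1² + s0² − 2ρ·s0·s1
- baseline-adjusted (ANCOVA, large samples): s1²(1 − ρ²)

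Hence raw minus ANCOVA is ρ²·s1², and change minus ANCOVA is (s0 − ρ·s1)² = s0²(1 − β)². Neither can be negative. The second is zero when β = 1.

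**Results with s0 = 10.**

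| s1/s0 | ρ | β | raw | change | ANCOVA | ANCOVA/raw | ANCOVA/change |
|---|---|---|---|---|---|---|---|
| 1.0 | 0.4 | 0.40 | 100 | 120 | 84 | 0.84 | 0.70 |
| 1.0 | 0.5 | 0.50 | 100 | 100 | 75 | 0.75 | 0.75 |
| 1.0 | 0.7 | 0.70 | 100 | 60 | 51 | 0.51 | 0.85 |
| 1.5 | 0.4 | 0.60 | 225 | 205 | 189 | 0.84 | 0.92 |
| 1.5 | 0.6 | 0.90 | 225 | 145 | 144 | 0.64 | 0.993 |
| 1.8 | 0.4 | 0.72 | 324 | 280 | 272.2 | 0.84 | 0.972 |
| 1.8 | 0.6 | 1.08 | 324 | 208 | 207.4 | 0.64 | 0.997 |

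- Against the raw score, adjustment removes 16% of the variance at ρ = 0.4 and 49% at ρ = 0.7.
- Against a change score with equal SDs, it removes 30% and 15%. This equals 1/0.70 = 1.43 and 1/0.85 = 1.18, that is 43% and 18% more patients.
- With the larger follow-up SD, the gain over a change score is 0.3%–8% in the four cases shown. It vanishes where β is exactly 1, for example at ratio 1.8 with ρ = 1/1.8 = 0.56.

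**Chance imbalance.** At 53 per arm the baseline difference between arms has SD √(2/53) = 0.19 baseline SDs, a 95% range of about ±0.38. With equal SDs, the share carried into the estimate is ρ for the raw score and ρ − 1 for the change score. A simulation of 20,000 trials at each of ρ = 0.3, 0.5 and 0.7 gave +0.30, +0.50 and +0.70 for raw, −0.70, −0.50 and −0.30 for change, and 0.00 for ANCOVA. At ρ = 0.5, an imbalance of 0.38 SD would thus shift the estimate by 0.5 × 0.38 = 0.19 SD, in opposite directions under the two readings.

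**The case against.** The strongest reply is that the plan already contains a linear mixed model. With t0 as a covariate, or with baseline means constrained equal, that model would recover most or all of the gain. How t0 enters is a detail that an article may leave to its analysis plan. This stands in part: a reader might infer that baseline is ignored in every analysis, and the document does not support that. The point is narrower. The article itself fixes an unadjusted two-sample test as the comparison at t3 and t4 and does not say that the mixed model replaces it. A mixed model with a free baseline would also behave much like a change score.

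Other limits stand as well:

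- A reader might infer biased results or an inflated error rate. Randomisation keeps the type I error correct on average. The imbalance is random and matters only as noise and as bias conditional on the arms actually drawn.
- A reader might infer that a change score always over-corrects. It does so only when ρ·s1/s0 is below 1, and that quantity runs from 0.60 to 1.08 in the unequal-SD cases.
- FMA-UE 0–35 is the permitted entry range, not an observed spread. Scores could cluster low, which would weaken the correlation.
- MAS and REPAS may vary little at 24–72 h, since spasticity is treated as something to be prevented. The gain there may be small. MAS is also ordinal, so a linear model is only approximate.
- These are secondary outcomes in a trial described as exploratory and as a pilot.

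None of this favours the unadjusted test, since in large samples ANCOVA is not less precise than either alternative.

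**Conclusion.** The point holds as one of efficiency and of robustness to chance imbalance, not of validity. It applies mainly to FMA-UE, the Action Research Arm Test and the Barthel Index, and probably with smaller benefit to MAS and REPAS. It does not extend to pain.

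The size rests on assumed correlations and SD ratios. It is substantial if the raw follow-up score is what is tested. If the change score is tested, it ranges from moderate with equal SDs to negligible when the slope on baseline is near 1. The documents therefore do not establish that a large loss will occur. They do show that a nearly free improvement is not in the stated comparison. No conclusion on the primary endpoint changes. The amendment is worth making but not critical.

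**What to change.** In Statistical Analysis, replace the two-sample test as the stated between-arm comparison of secondary outcomes at t3 and t4 with a baseline-adjusted model, in either of two forms:

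- ANCOVA of the follow-up score on arm, the patient's own t0 score and sex (the minimisation factor); or
- the linear mixed model already planned, with t0 as a covariate or baseline means constrained equal, plus sex, giving the arm contrast at t3 and at t4.

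Report the adjusted arm difference with its 95% CI. For MAS, use an ordinal or rank-based baseline-adjusted analysis if a linear model fits poorly.

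Cost: a change of wording before unblinding, slightly more analysis work, and a modelling assumption about the relation to baseline. All the values needed are already collected at t0.

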## Abstract

**Background:**

Stroke is one of the most frequent causes of death and disability worldwide. It is accompanied by the impaired motor function of the upper extremities in over 69% of patients up to hemiplegia in the following 5 years in 56% of cases. This condition often is characterized by chronic poststroke pain, difficult to manage, further worsening quality of life. Poststroke pain occurs within 3–6 months. Robot-assisted neurorehabilitation using the Automatic Recovery Arm Motility Integrated System (ARAMIS) has proven efficacy in motor function recovery exploiting the movements and the strength of the unaffected arm. The rationale of the ROBOCOP (ROBOtic Care of Poststroke pain) randomized trial is the assessment of the impact of robot-assisted functional and motor recovery on the prevention of poststroke pain.

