## Introduction

### Background and Rationale

Stroke represents one of the most serious causes of death and disability-adjusted life-years lost (1) destined to keep increasing due to global aging. One of the most common long-term disabilities occurring in over 69% of cerebrovascular lesions consists of impaired motor function of the upper extremities up to hemiplegia in the following 5 years in 56% of cases (2, 3). Stroke is complicated by the occurrence of poststroke pain usually within 6 months from the acute event (4), with poststroke pain syndromes reported in up to 30%−40% of stroke outliving patients (5), chronic in 11–55% of patients (6). The latter include pain caused by different pathophysiology in which nociceptive and neuropathic features can coexist ranging from pain secondary to spasticity, shoulder pain, complex regional pain syndrome (CRPS), and headache, in 1 out of 10 stroke sufferers, that is, migraine-like in 31.3% cases (7), to central poststroke pain (8). Shoulder pain is the most frequent affecting some 30–40% of stroke survivors (6). Lenticulocapsular strokes can cause hemiparesis with consequent shoulder pain (9). The development of poststroke pain correlates to the severity of stroke and paresis is associated with a 3.1-fold higher risk for stroke-related pain (10). Unfortunately, often patients suffering from pain after stroke do not find relief in current analgesic treatment because it is not supported by clinical trials, as a consequence, guidelines are lacking (9). In fact, the systematic review and meta-analysis of literature has highlighted that very few clinical trials assess the efficacy of opioids, the most potent analgesics on poststroke pain, the number of patients is very small and these studies have not been designed specifically for this condition, thus usually not evaluating the correlation between rehabilitation, pain, and physical functioning after stroke (11). Actually, stroke survivors do not even benefit from clinical trials on the novel preventative treatment of migraine, e.g., the anticalcitonin gene-related peptide monoclonal antibody eptinezumab that can provide rapid and longer-lasting action (12). This is often due to the lack of use of pain scales for an objective pain assessment validated in specific populations, e.g., patients affected by stroke, and this problem becomes even more worrying for patients with aphasia and noncommunicative and in the pandemic emergency (13–16). Robot-assisted neurorehabilitation for patients with stroke having the Integrated Robotic System for Stroke (IRSS) prototype Automatic Recovery Arm Motility Integrated System (ARAMIS) has provided a significant improvement of motor recovery (17). It consists of two computer-controlled, symmetric, and interacting exoskeletons that impress to the paretic arm the same strength and movement of the healthy arm and it has been validated in stroke survivors. The rationale for the use of ARAMIS in poststroke neurorehabilitation of the paretic upper limb relies on the possible prevention of aberrant early plasticity. According to our working hypothesis, ARAMIS might improve plasticity in agreement with the concept underlying the Reinforcement-Induced Movement Therapy (18), avoiding the occurrence of spasticity and hypotonia.

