### Sample Size

The calculation of the sample power is based on literature data (25, 36–40) to obtain 25% of improvement in the primary endpoint using G^*^Power 3.1.9.7 (41). The formula for calculating the sample size is given, for two arms of the same size, as it follows:

$$\begin{array}{l} n=\left[{\left(Z_{\alpha /2}+Z_{\beta }\right)}^{2}\times \left(2{\left(\sigma \right)}^{2}\right)\right]/{\left(\mu 1-\mu 2\right)}^{2} \end{array}$$

where,

*n* = sample size required in each group;

*Z*_α/2_ = 1.96, according to 5% level of significance;

*Z*_β_ = 0.84 for 80% power;

σ = standard deviation;

μ1 – μ2 = primary outcome measures significant difference = 6.34 with ARAMIS and 5.4 with conventional rehabilitation (25);

*d* = 0.3.

Therefore, considering a 95% confidence level and a study power of 80% (42), the result will be *n* = 53 per arm.

Adjusted sample size *n*_1_ to account for potential drop-out rates is *n*_1_ = *n*/(1–*d*), where *d* = 10% (43), thus *n*_1_ = 118 patients will be recruited, 59 per each arm.

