## Discussion

Cerebrovascular accidents are often accompanied by motor disability and chronic pain. Poststroke pain consists of complex syndromes including both nociceptive musculoskeletal and neuropathic features (49). Due to its characteristics, poststroke pain is often underdiagnosed and unrelieved (50). The best management option for chronic pain consists of its prevention. To this aim, this is the first clinical trial to study the use of an IRSS in subacute neurorehabilitation after stroke. In particular, ARAMIS has provided more efficacy than conventional poststroke neurorehabilitation when applied for 7–8 weeks in the improvement of motor function and activities of daily living (17, 25, 51, 52). When the lesion is high after lateral medullary infarction, known as Wallenberg's syndrome, or in the ventroposterior part of the thalamus, central poststroke pain ensues (6). In the event hemiparesis occurs, the healthy arm may offset the effect of spasticity and locomotion (52, 53). Within this frame, ARAMIS may prevent central pain, and, concurrently, may drive correct re-organization in hemiplegic patients capturing the motions and the strength of the unaffected upper limb. In fact, ARAMIS consists of two exoskeletons with 6 degrees of freedom driven by two engines and controlling the shoulder joints to compensate for the inadequate motility and strength of the paretic arm (51). Robot-assisted motor rehabilitation and myoelectrical stimulation are demonstrated to provide reduction of the upper limb impairment (38, 39, 54–56) and pain improvement (40, 57, 58). Also, actigraphic measure systems can predict acute phase stroke prognosis (59), supporting the role of technological progress in stroke. Furthermore, the use of these devices can help the familiarization of poststroke survivors with the latter technology (60). However, a decrease in upper limb impairment does not always correlate to practical and daily functional improvement and this translational aspect needs to be studied for effective neurorehabilitation (61). In fact, the wide multicenter trial for the evaluation of robot-assisted training for the upper limb after stroke (RATULS) has demonstrated that robotic neurorehabilitation does not significantly improve the upper limb function (62). Pain intensity has been positively correlated with time since stroke and negatively with motor function (44), supporting the need to examine the role of robot-assisted rehabilitation in pain processing and to clear the mechanisms necessary for effective functional gain. The latter is a top ten priority for stroke survivors (63). Therefore, the role of ARAMIS-assisted neurorehabilitation in the prevention of poststroke pain occurring 3–6 months after stroke deserves investigation. The efficacy of robot-assisted neurorehabilitation in the prevention of chronic poststroke pain could pose the basis for a remarkable improvement of stroke sufferers' quality of life. Moreover, a better and deeper understanding of robot-related motor learning is needed (55) and, although the stage is a predictor for better rehabilitation outcomes, IRSS neurorehabilitation, without significant differences among the several devices existing (64), has proven promising results also in chronic stroke survivors (65). In this already fragile population, robot-assisted rehabilitation may also reduce the use of analgesics known to be endowed with serious side effects. In fact, fragile populations are often subjected to limited and inappropriate pain treatment (66–68). The next step will consist in investigating the effect of this neurorehabilitation procedure on the use of analgesics, both synthetic and of natural origin, as the essential oil of bergamot endowed with analgesic (69) and flumazenil insensitive anxiolytic-like (70) properties and which has been engineered allowing double-blind clinical trials (71, 72).

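### The planned pain–recovery correlation is not adjusted for FMA-UE at entry, so it cannot separate initial severity from recovery

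*Protocol article*

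**What the plan says.** In the protocol article, Statistical Analysis plans "The correlation between pain (VAS measure) and recovery (FMA-UE), assessed at" t0, t1, t2, t3 and t4, and says that it "will be performed through the Pearson product-moment correlation coefficient". The general threshold is "Values of *p* < 0.05 will be considered statistically significant". No change score, partial correlation or covariate is named for this analysis. The comparison of t3 and t4 with t0 in the same section belongs to the between-arm tests of the outcomes.

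Three other places bear on it:

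- The abstract gives the rationale as "assessment of the impact of robot-assisted functional and motor recovery on the prevention of poststroke pain".
- Background and Rationale says "The development of poststroke pain correlates to the severity of stroke", and the Discussion adds "Pain intensity has been positively correlated with time since stroke and negatively with motor function".
- Eligibility Criteria admits FMA-UE scores from 0 to 35 and requires that the hemiplegic arm be free of pain at baseline.

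**The concern.** The variable treated as recovery is the score on the day. Two features show this: t0 is among the listed time points, and no gain exists at t0; and the reference to t0 as comparator is attached to a different analysis. A score at t3 or t4 is the entry score plus the gain. If patients who enter with poorer arm function later have more pain, as the severity correlation reported in the Introduction suggests, they will show both lower FMA-UE and higher VAS at follow-up, whether or not gain matters for pain. The resulting r is negative, which is the direction the working hypothesis predicts.

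The between-arm tests and the mixed model treat the outcomes separately. This correlation is the only stated analysis that links motor recovery to pain within patients. The Objectives section presents the trial as a pilot on which later work will rest, so a correlation that reflects entry severity could be carried forward as evidence about recovery.

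**Working it through.** The plan states no figure for this correlation, so there is none to reproduce. The question is how often the planned test would be significant when gain is unrelated to pain.

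**Inputs from the protocol article**

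- Evaluable patients: Sample Size gives "considering a 95% confidence level and a study power of 80% (42), the result will be *n* = 53 per arm", so N = 2 × 53 = 106. With dropout, 53/(1 − 0.10) ≈ 59 per arm, or 118 recruited. N = 106 is taken as given; nothing below depends on how 53 was reached.
- Test: p < 0.05. Two-sided is assumed, in line with "1.96, according to 5% level of significance" in Sample Size.

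**Inputs the documents do not give (assumed)**

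- ρ, the correlation of entry FMA-UE with later VAS: −0.1 to −0.5.
- k, the SD of the gain divided by the SD of entry FMA-UE: 0.5, 1.0 or 1.5.
- Gain unrelated to the entry score, and VAS unrelated to gain given the entry score.

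**Step 1: significance bound.** The critical |r| is 0.191 at N = 106 (0.181 at N = 118).

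**Step 2: induced correlation.** Under these assumptions the correlation of entry with follow-up FMA-UE is 1/√(1 + k²), and the induced r between follow-up FMA-UE and VAS is ρ/√(1 + k²). If the entry–follow-up correlation is 0.6 (k ≈ 1.33):

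- ρ = −0.4: r = −0.4 × 0.6 = −0.24. Fisher z = 0.2448; 0.2448 × √(106 − 3) = 2.48; Φ(2.48 − 1.96) ≈ 0.70.
- ρ = −0.3: r = −0.3 × 0.6 = −0.18, which gives about 0.45.

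**Step 3: simulation over the range.** Share of trials with p < 0.05 for the raw level correlation, N = 106:

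| ρ | k = 0.5 | k = 1.0 | k = 1.5 |
|---|---|---|---|
| −0.1 | 14% | 11% | 8% |
| −0.2 | 45% | 30% | 20% |
| −0.3 | 80% | 60% | 42% |
| −0.4 | 97% | 84% | 64% |
| −0.5 | 99.8% | 96% | 82% |

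The mean r is negative in every cell: higher FMA-UE goes with less pain.

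**Step 4: skewed VAS.** A version with many zero VAS values gives the same pattern (assumed: entry FMA-UE uniform on 0 to 35, about 35% with pain, gain SD 5 or 10 points). The raw correlation is significant in 15–21%, 45–66% and 89–98% of trials at assumed pain odds ratios of 1.35, 1.82 and 3.1 per 10 FMA-UE points lower at entry.

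**Step 5: alternatives.** The partial correlation given t0 FMA-UE is significant in 4–6% of trials in every scenario. The unadjusted correlation with gain stays near 5% only while gain is unrelated to entry score. With a slope of gain on entry score of +0.3 or −0.3, it ranges from 5% to 77%.

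**Step 6: level or gain.** Write FMA_t = FMA_0 + G. Then a + b·FMA_t + c·FMA_0 = a + b·G + (b + c)·FMA_0. Once FMA_0 is in the model, the coefficient b is the same for level and for gain. The missing element is the baseline adjustment.

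**Step 7: t0.** Freedom from limb pain is an entry condition, so VAS has essentially no spread at t0, and no recovery has taken place. The coefficient at t0 is undefined or uninformative.

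**The case against.** The strongest reply is that the plan promises a correlation and would deliver one. If patients with better arm function have less pain, that association is real, and the section attaches no causal conclusion to it. This stands as far as it goes. The difficulty is that the plan names the score recovery, and a level cannot carry that meaning.

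A second reply is that an article may leave covariates and derived variables to a fuller plan. That would cover silence. Here the variables, time points and coefficient are all named, and the inclusion of t0 fits only the level. One could read the time points as merely saying when the scales are administered, but the sentence would still name no baseline adjustment.

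Three stronger readings may tempt a reader, and the documents do not support them:

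- *That the protocol says severity drives pain.* It reports correlations only. Its 3.1-fold risk concerns having paresis, which every enrolled patient has, so it gives no gradient within this trial.
- *That the trial's main test is compromised.* The main test is the randomised comparison of pain between arms, which does not use this correlation. The trial is also described as exploratory.
- *That arm differences are certainly mixed in.* The section does not say whether r is computed over both arms or within each. Adjusting for arm settles the matter either way.

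**Conclusion.** The point holds for a supporting analysis. As written, the pain–recovery correlation cannot distinguish initial severity from recovery, and it can reach p < 0.05 when gain is unrelated to pain. The size is unknown from the documents. The range of about 8% to over 99% rests entirely on the assumed ρ and k, with 106 patients and gain unrelated to entry score. At ρ = −0.1 the excess over 5% is small, and from ρ = −0.3 it is large. Restricting entry to FMA-UE 0–35 narrows the spread of severity but does not remove it.

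A reader might conclude that the remedy is simply to correlate VAS with gain. That is not sufficient, because a gain that depends on the entry score brings severity back in.

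**What to change.** For the pain–recovery association, replace the raw Pearson coefficient by a partial correlation, or by a regression of VAS at t3 and at t4 on FMA-UE with t0 FMA-UE and arm as covariates. FMA-UE may enter as level or as change from t0. Report the estimate with its 95% CI and describe it as an observational association: motor gain arises after randomisation, and the adjustment covers only the severity that t0 FMA-UE captures. Drop the correlation at t0.

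The cost is a change of wording in Statistical Analysis. All the data are already to be collected, and neither the sample size nor the visit schedule changes.
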